### **2.4.2 Source of self-efficacy (Lenz & Shortridge-Baggett, 2002)**

Self-efficacy are influenced by four main important sources of information which are performance accomplishments: practicing and earlier experiences, vicarious experience: observation of others, verbal persuasion and physiological information: self-evaluation of physiological and emotional states.

#### **Performance accomplishments: practicing and earlier experiences**

Practicing is the most important source of self-efficacy because it based on a person's experience. Experiences of success (the feeling of mastery) enhance self-efficacy, while regular failure decreases self-efficacy, especially when the failure takes place early in learning process. Once a person has developed a strong self-efficacy, one failure does not have much influences.

#### **Vicarious experience: observation of others**

Seeing others perform successfully also is an important source of self-efficacy. Other persons can serve as example (role models) and supply information about the degree of difficulty of a specific kind of behaviour. The people serving as role models, however should show similarity to the observer in those characteristics which are relevant to the issue.

#### **Verbal persuasion**

Verbal persuasion is the most often used source of self-efficacy, because it is easy to use. By giving instructions, suggestion and advice, health care providers try to convince persons that they can succeed in a difficult task. For critical importance are the credibility, expertise, trustworthiness and prestige of the person doing the verbal persuasion.

#### **Physiological information: self-evaluation of physiological and emotional states**

Information on the human body can also influence a person's estimation of the capability to show a specific behaviour. In judging their own capacities persons use information about their physiological and emotional situations. They experience tension, anxiety and depression as signs of personal deficiency. In activities that require strength and perseverance, they interpret fatigue, pain, hypoglycaemia as indicators of low physical efficacy. Stress can have a negative influence on self-efficacy.

### 2.4.3 Methods for increasing self-efficacy

Self-efficacy can be increased in several ways, including; by providing clear instructions, providing the opportunity for skill development or training, and modelling the desired behavior (MOH New Zealand, 2011). There are four components to increase Self-efficacy level; mastery experience, modelling, improving physical and emotional states and verbal persuasion (Bandura, 1997) (Table 2.3).

Table 2.3 Methods for increasing self-efficacy  
source Bandura, (1997)

|                                         |                                                                                                                                                                                                                                                 |
|-----------------------------------------|-------------------------------------------------------------------------------------------------------------------------------------------------------------------------------------------------------------------------------------------------|
| Mastery experience                      | Enabling the person to succeed in attainable but increasing challenging performances of desired behaviours. The experience of performance mastery is the strongest influence on self-efficacy belief.                                           |
| Modelling                               | Showing the person that others like themselves can do it. This should include detailed demonstrations of the small steps taken in the attainment of a complex objective (social modelling) or by giving them a brochure as a symbolic modelling |
| Improving physical and emotional states | Making sure person are well-rested and relaxed before attempting a new behaviour. This can include efforts to reduce stress and depression while building positive emotions- as “fear” is re-labelled as “excitement.”                          |
| Verbal persuasion                       | Telling the person that he or she can do it. Strong encouragement can boost confidence enough to induce the first efforts toward behaviour change.                                                                                              |

### 2.5 Previous studies related to self-efficacy and self-care behaviour in diabetes management

The self-care behaviour for diabetes provide useful context in which to examine the role of self-efficacy beliefs in adherence to prevention behaviours (Maddux, 1995; Sarkar, Fisher, & Schillinger, 2006; Rodriguez, 2013). This concept was introduced from Social Cognitive Theory (SCT) in health promotion and patient education program (Bandura, 1977; Bandura, 1989; Bandura, 2004) and has been increasingly applied, both as a model of health behaviour and as a framework for developing effective health intervention in various population.

Self-efficacy is a major predictor of successful self-care behaviour in diabetes management because it will influences how people think, motivate themselves and act in order to modifying health behaviour in the desired direction (Bandura, 1997; Lenz & Shortridge-Baggett, 2002). The Self-efficacy model is suited to create educational programs to improve self-care behaviour of patients with diabetes (van der Bijl et al, 2001; McDowell et al, 2005). Wu et al. (2007) stated by enhancing self-efficacy towards self-managing the disease can be an effective way to improve disease control and to understand adherence to self-care behaviour.

Previous research findings have focused on knowledge of patients with diabetes to control the disease, but Hurley and Shea (1992) stated having knowledge does not necessarily change patients' behaviour. The evolution of research was then extended to view the other aspects that can change the behaviour. The self-efficacy concept related to patients who feel more confident if they are able to succeed at the task of self-care behaviour (Wolf, 2006). Thus, self-efficacy and self-care behaviour was identified as a key psychosocial variable related to diabetes self-management. Greater self-efficacy was a significant predictor of better self-care behavior (Johnston-Brooks et al., 2002). Furthermore, by enhancing self-efficacy in elderly with diabetes may increase the self-care behaviour by behavioural change strategies (Shi, Ostwald & Wang, 2010). Literature reviews showed by integrating self-efficacy theory and self-care behaviour in patients with diabetes appears to enhance patients' positive outcome.

In the past, Hurley and Shea (1992) conducted study on self-efficacy: strategy for enhancing diabetes self-care in the United States. This study found that patients with higher levels of self-efficacy were better able to manage their diabetes self-care behaviour. However, there is need for further research to be conducted in different places due to the homogeneity of the subjects. This cross sectional study focused on individuals who used insulin and the small sample of respondents involved between the high socioeconomic status only and lack of multi-ethnicity. This finding might also be invalid now as it was done a long time ago.

Wang and Shiu (2004) conducted a study on diabetes self-efficacy and self-care behaviour of Chinese patients living in Shanghai. The results shows patients with higher levels of self-efficacy reported that they were better able to manage their diabetes self-care. Limitation found in the study was when the researchers employed a small sample size in one clinic only and the result was difficult to generalize to other parts of the population. However, this finding lends support to the importance of incorporating the concept of self-efficacy in the design and implementation of diabetes nursing interventions.

Subsequently, Strurt et al., (2006) conducted study on complex intervention development for diabetes self-management in United Kingdom. The aim of this randomized controlled trial is to present the development and evaluation of the Self-Efficacy Goal Achievement (SEGA) nursing intervention for diabetes. It is a robust study showed an increase in patient self-efficacy and life satisfaction. However, the diabetes self-management is general rather than focusing specifically on foot care aspects.

Furthermore, Wu et al. (2007) conducted a cross sectional study on self-efficacy, outcome expectations and self-care behaviour in people with diabetes in Taiwan. The findings supported the use of the self-efficacy model as a framework for understanding adherence to self-care behaviour. The result was difficult to generalize because it employed a small sample from one clinic and not focusing on foot self-care behaviour itself.

A cross sectional study on foot-care self-efficacy and foot-care behaviour in people with peripheral neuropathy in Australia (Perrin et al., 2009). There is an association between foot-care self-efficacy and foot-care behaviour. However, the sample size was small (95 respondents) as results cannot be generalized. The foot

care behaviour scale used in this study has some decent content validity, it has not been comprehensively validated, and the scoring system is overly complicated.

Another study on foot care education and self-management behaviors in diverse veterans with diabetes by (Olson et al., 2009). This research builds on self-efficacy and self-management theory and the finding suggests the need for culturally-specific self-management education to address unique cultural preferences and barriers to care.

Shi et al., (2010) examined the effect of a hospital-based clinic intervention on glycaemic control self-efficacy and glycaemic control behaviour of patients with diabetes in China. The findings revealed that the experimental group showed statistically significant improvement in glycaemic control self-efficacy and glycaemic control behaviour immediately and four months after the intervention. However, the study does not mentioned about improvement specifically in foot self-care behaviour scores.

A descriptive study was done on relationship between foot-care self-efficacy beliefs and self-care behaviours in diabetic patients in Iran (Hamedan et al., 2012). Result shows foot self-efficacy is a predictor of good self-care behaviours. It was suggested that older diabetic patients should be advised to perform self-care behaviour and assessed for self-efficacy because they have many problems in self-care.

There is a local study on self-efficacy and self-care behaviour of Malaysian patients with type 2 diabetes (Sharoni & Wu, 2012). The finding suggested that self-efficacy can be used as a model to understand self-care behaviour. Limitation in this cross sectional survey appeared when this study is conducted only in one hospital and the convenience sampling may not represent the whole Malaysian with diabetes.

Chin, Huang, & Hsu, (2013) conducted a study on impact of action cues, self-efficacy and perceived barriers on daily foot exam practice in type 2 diabetes mellitus patients with peripheral neuropathy in Taiwan. This study suggests the health professionals to design interventions that aim to promote daily foot-exam practice. The cross sectional study design may inhibits the information about cause and effect relationship.

Fan, Sidani, Cooper-Brathwaite, & Metcalfe, (2013) conducted a study on improving foot self-care knowledge, self-efficacy, and behaviors in patients with type 2 diabetes at low risk for foot ulceration. The findings in this pilot study indicated that the foot self-care educational intervention was effective in improving foot self-care knowledge, self-efficacy and behaviors in adult patients with type 2 diabetes at low risk for foot ulceration. However, the study is not a randomized controlled trials design, not focus among elderly population and the conveniences sampling may leads to bias.

All of the previous researchers have established similar findings from their studies and proved the importance of self-efficacy and self-care behaviour in patients with diabetes in various areas. For patients with diabetes to carry out a high level of self-care behaviour, they must acquire a high self-efficacy in their ability for disease management (Wangberg, 2007). However, there are some limitations from the previous studies such as; study design does not explain on cause and effect

relationship, inadequate sample size, nonprobability sampling and study was conducted long time ago. Thus, this study proposed to contribute more information to existing theory in our local setting focusing on self-efficacy and foot self-care behaviour among elderly population in institutionalized care. By integrating the Self-efficacy model in foot self-care behaviour program may increase the confidence level and self-compliance in caring the feet among elderly with diabetes.

## **2.6 A new conceptual framework; the self-efficacy enhancing program on foot self-care behaviour of elderly with diabetes**

The rational for developing the self-efficacy enhancing program is to improve self-care behaviour of elderly with diabetes in taking care of their feet. As the person become older, they need to stay healthy and being independently. This behaviour can improve the health outcome and reduce the complication rate related to diabetes foot problems. The self-efficacy enhancing program is to empower the elderly with diabetes to perform foot self-care behaviour effectively.

Previous literatures show there was a significant relationship between self-efficacy and self-care behaviour of patients with diabetes. Self-efficacy has been demonstrated as a main predictor in promoting self-care behaviour by behaviour change. In this study, the development of self-efficacy enhancing program on foot self-care behaviour of elderly with diabetes are designed via new conceptual framework based on Self-efficacy theory (Bandura, 1977). For example, a person to perform foot care (behaviour) for health reasons (prevent foot complication (outcome), he must believe both that foot care will benefit his foot health (foot care outcome expectation) and also that he is capable of practicing foot care (foot care efficacy expectation).

The main reason for the development of self-efficacy enhancing program is to improve foot self-care behaviour of elderly with diabetes and to prevent feet complications related to diabetes. In Malaysia, least researchers are engaged in theory based interventions in relation to diabetes foot self-care behaviour. Thus, by introducing new diabetes educational program may improve current traditional educational program given from health care provider.

The self-efficacy enhancing program on foot self-care behaviour of elderly with diabetes is an important part in this framework (Figure 2.3). Strategies to implement the self-efficacy enhancing program are described below are derived from the nursing process (Berman & Snyder, 2012).

Firstly, demographic factors (e.g. age, ethnicity, gender, education level, marital status, number of children and patterns of living) and clinical characteristics may influence the foot self-care behaviour. In this phase patients' demographic data, clinical characteristics, independent level, cognitive level and depression will be gathered. The data will be collected through questionnaire form and blood tests.

Subsequently, both elderly with diabetes and health provider will make a specific judgment about current problem in relation to diabetes foot problems. This involves actual and potential issues whether an elderly with diabetes is at risk to

develop any problem. During this phase also, elderly with diabetes will be assessed on current behaviour on foot self-care, readiness and preparedness for health improvement in their feet. This will be measured with the scaling question on foot self-care behaviour, foot care efficacy expectation, foot care outcome expectation, knowledge on foot care and quality of life.

A plan of action will be developed after both an elderly with diabetes and nurses have set the diagnosis. Self-efficacy goals and take a strategic action must come from general to specific. For example, foot self-care behaviour, inspection on feet might be a goal but it needs more detail about the steps and objectives on how they check on their own feet. Guide the elderly with diabetes to set clear, realistic and achievable targets for the expected good outcome according to time frame.

Implementation phase is where elderly with diabetes perform the goal of desired behaviour that has been established in planning phase. For example, health provider will educate, counsel and inspire the elderly with diabetes about foot self-care behaviour. The health provider will integrate the Self-efficacy theory to enhance of good foot self-care behaviour for the elderly with diabetes along the program. Activities in this session will involves on seminar presentation, diary, serial visits, telephone and/or short message service (SMS) follow up. During this time, the elderly with diabetes will implement the foot self-care behaviour with self-confident independently. The health provider should be bear in mind that other variables such as foot care efficacy expectation, foot care outcome expectation, knowledge and quality of life are the factors may influence the successfulness of the foot self-care behaviour intervention program.

This evaluation is the last phase, where health provider and elderly with diabetes will determine the goals is achieved or not. The primary outcomes is the foot self-care behaviour will be improved, the foot self-care behaviour worse, or there is no significant difference of foot self-care behaviour before and after implementation phase. The secondary outcome are level of foot care efficacy expectation, foot care outcome expectation, knowledge on foot care and quality of life. During this phase the effectiveness of the program will be assessed through the questionnaire form of quality of life, knowledge on foot care, foot care efficacy expectation, foot care outcome expectation and foot self-care behaviour.

[figure not shown]

Figure 2.3 The conceptual framework for development and evaluation self-efficacy enhancing program on foot self-care behaviour of elderly with diabetes

## 2.7 Summary

Assisting elderly with diabetes to change their foot self-care behaviour is an important nursing role in achieving the highest possible of health outcome. There is increasing evidence that a vital component in health-related activities change is the perceived self-efficacy of the patients to behave differently. This chapter has highlighted the areas self-efficacy and foot self-care behaviour. The next chapter will discuss the methods used in this study.

## Chapter 3

### METHODOLOGY

#### 3.1 Introduction

This chapter will discuss in detail on how the study will be conducted. It will include the study setting, design, population, sample, instrument used, data collection methods, data analysis, ethical consideration and pilot study.

#### 3.2 Study setting

This study will be conducted in the institutional care for elderly named Rumah Seri Kenangan (RSK), Peninsular Malaysia. The RSK is under government organization, Social Welfare Department of Malaysia (JKMM), Ministry of Women, Family and Community Development. There are eleven RSKs in Malaysia, nine in Peninsular Malaysia and two in East Malaysia; RSK Bedong, Kedah, RSK Tanjong Rambutan, Perak, RSK Seremban, Negeri Sembilan, RSK Johor Bharu, Johor, RSK Kangar, Perlis, RSK Taiping, Perak, RSK Cheras, Selangor, RSK Cheng, Melaka, RSK Taman Kemumin, Kelantan, RSK Kuching and RSK Sibu. There are approximately 130 – 250 residents staying in each RSK. Figure 3.1 shows the location of RSK in Peninsular Malaysia.

[figure not shown]

Figure 3.1 The location of RSK in Peninsular Malaysia

### 3.3 Study design

The design used for this research is a Randomized Control Trial (RCT) design with two groups; intervention and control, measurements will be completed before intervention and after intervention. In this single blind study, only the researcher is able to differentiate which group are under intervention or control group. The respondent will not be informed whether they are categorized under intervention or control group.

The intervention group will receive a self-efficacy enhancing program on foot self-care behaviour while the control group will receive a usual health care. The aim of the education program will that, after completed the program, the foot self-care behaviour, foot efficacy expectation, foot outcome expectation, knowledge on foot care and quality of life will be improved with respect to the program delivered. However, after the data collection process completed, the control group will be given the same program as the intervention group.

### 3.4 Population

#### 3.4.1 Targeted population

There are approximately 1631 of residents staying in Peninsular RSK (Table 3.1). Currently the RSK Seremban was closed due to renovation. Majority of them are independent and able to perform their activity daily living (e.g. bathing, eating, grooming, etc.) independently. The targeted population in this study is, the respondents (elderly with diabetes) must be diagnosed with diabetes. The number of elderly diagnosed with diabetes who are totally independent in each RSK is about 40-50 residents.

Table 3.1 Number of RSK Inmates by Institution and Sex, 2013  
source: Jabatan Kebajikan Masyarakat, Malaysia

| Institution          | Male       | Female     |
|----------------------|------------|------------|
| RSK Bedong           | 193        | 99         |
| RSK Cheng            | 103        | 84         |
| RSK Cheras           | 97         | 78         |
| RSK Pengkalan Chepa  | 73         | 62         |
| RSK Johor Bahru      | 176        | 102        |
| RSK Kangar           | 72         | 74         |
| RSK Seremban         | 0          | 0          |
| RSK Taiping          | 94         | 79         |
| RSK Tanjung Rambutan | 164        | 81         |
| Total         | 972 | 659 |

### 3.5 Sample

#### 3.5.1 Sampling method

A probability cluster sampling with specific eligibility criteria will be used in this study. There are nine RSK in the Peninsular Malaysia. However, for the time being, RSK Negeri Sembilan was closed due to renovation process, so there are total eight of RSK in Peninsular Malaysia. RSK Cheras will be excluded for pilot testing and RSK Pengkalan Chepa located in West Peninsular Malaysia. Hence, six RSK will be allocated randomly using random sequence number generator where each group (RSK) is having equal chance to be neither in the intervention group nor control group. Here, there are three RSK will be taken in intervention group and another three RSK will be placed under control group. Figure 3.2 showed how the sample will be selected and grouped in this study.

[figure not shown]

Figure 3.2 Sampling selection process

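### Six homes are randomised 3:3 with no balancing, leaving a 1-in-10 chance that the three largest and most male homes all fall in one arm

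*Combined protocol and SAP*

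**What the plan says.** Section 3.5.1 (Sampling method) makes the home the unit of allocation: "six RSK will be allocated randomly using random sequence number generator". The one constraint stated is the number of homes per arm: "there are three RSK will be taken in intervention group and another three RSK will be placed under control group". Each home is meant to have an equal chance of either arm. The section names no stratification, matching or minimisation. One home is closed, and two more are left out: "RSK Cheras will be excluded for pilot testing and RSK Pengkalan Chepa located in West Peninsular Malaysia". Figure 3.2 is not shown in the text reviewed, so this reading rests on the wording of 3.5.1.

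Other places bear on the point:

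- Section 3.4.1, Table 3.1 ("Number of RSK Inmates by Institution and Sex, 2013") gives the men and women in each home. The same section puts independent residents with diabetes at about 40-50 in every home.
- Section 2.6 lists gender among the demographic factors that may influence foot self-care behaviour, which it names as the primary outcome.
- Section 3.9 and Table 3.5 plan a mixed ANOVA of group by time, with no term for home, sex or home size.

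**The concern.** With six units, simple randomisation cannot be relied on to balance anything. Home size and sex mix are known before the draw and are not used, and in this set of homes they run together: the large homes are the more male ones. If those three homes land in one arm, large-versus-small status and treatment arm become the same variable. No later analysis could then tell a difference between home types from an effect of the program.

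Home conditions could plausibly matter. Under section 3.7.2, staff in the intervention homes are asked to remind respondents every day, and the weekly follow-up call goes to them. The documents give no staffing figures by home, so this is a possible mechanism only. Neither the allocation nor the planned ANOVA guards against it.

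**Working it through.** **Inputs.** All counts are from Table 3.1; for example, "RSK Bedong | 193 | 99" and "RSK Cheng | 103 | 84" are men then women. The table's own totals reproduce: 972 men + 659 women = 1631, the figure in section 3.4.1. The plan gives no figure for the chance of an unbalanced split.

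| Home | Men | Women | Total | % male |
|---|---|---|---|---|
| Bedong | 193 | 99 | 292 | 66.1 |
| Johor Bahru | 176 | 102 | 278 | 63.3 |
| Tanjung Rambutan | 164 | 81 | 245 | 66.9 |
| Cheng | 103 | 84 | 187 | 55.1 |
| Taiping | 94 | 79 | 173 | 54.3 |
| Kangar | 72 | 74 | 146 | 49.3 |

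The two sets are separate on both measures: 245 v 187 residents and 63.3% v 55.1% male at the boundary.

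**Chance of the extreme split.** The number of 3:3 allocations is C(6,3) = 20, all equally likely. Two of them put the three large homes together, one for each arm label: 2/20 = 10%.

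**Size of the imbalance in that case.**
- Large homes: 292 + 278 + 245 = 815 residents; 193 + 176 + 164 = 533 men; 533/815 = 65.4%.
- Small homes: 187 + 173 + 146 = 506 residents; 103 + 94 + 72 = 269 men; 269/506 = 53.2%.
- Gap: 12.2 percentage points.

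**With at least one large and one small home per arm.**
- Splits left: 20 - 2 = 18.
- Largest remaining male-share gap: Bedong, Cheng and Tanjung Rambutan (460/724 = 63.5%) against Johor Bahru, Kangar and Taiping (342/597 = 57.3%), or 6.2 points.
- Equal chance: every allowed split is allowed with the arm labels swapped, so each home is in the program arm in 9 of 18.
- Pairs of homes: any given pair shares an arm in 8 of the 20 splits. Two homes of the same type lose the 2 extreme splits and share an arm in 6 of 18. One large and one small home share an arm in 8 of 18. No pair is always together or always apart.
- Smallest two-sided permutation p over homes: 2/20 = 0.10 before, 2/18 = 0.11 after.

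**Recruited numbers.** At 40-50 eligible residents per home, any three homes hold 120 to 150, against a target of 71 per arm (section 3.5.2).

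**The case against.** The strongest reply is that 3:3 randomisation of homes without stratification is a legitimate choice. A 10% chance of imbalance is chance, not bias in the method, and nothing in the documents shows that sex or home size affects response to the program. That stands, and it limits how serious the point is.

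Several stronger readings are tempting, and the documents do not support them:

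- *The arms would be recruited very unequally.* A reader might scale the 142 respondents by home size: 142 x 815/1321 = 88 v 54. Section 3.4.1 speaks against this. It gives about 40-50 eligible residents in every home, whatever its size, so each arm can reach 71 under any split.
- *A sex imbalance could not be repaired.* It could. Both arms would hold many men and women even in the worst split, and the questionnaire records each respondent's gender, so a sex term could be added. On the planning figures in 3.5.2 (difference 3.90, SD 6.76), a 12.2-point gap would move the crude difference by 0.39, a tenth of the effect, only if men and women differed by 0.39/0.122 = 3.2 points, or 0.47 SD. Outcomes are also measured at baseline, so a stable difference between arms would be visible and is not the group-by-time effect.
- *The draw is wholly unrestricted.* The 3:3 split is fixed, and the 1-in-10 figure depends on it. Independent coin flips per home would give 2/64, or 1 in 32.

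It is also true that unmeasured home factors can be confounded with arm under any 3:3 split. What remains is narrower: one known home contrast can coincide exactly with arm, no adjustment could separate the two, and the draw can rule this out in advance at almost no cost.

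**Conclusion.** The point holds as a cheap improvement to the design. There is a 10% chance that arm equals home type (815 v 506 residents in the source homes, 65.4% v 53.2% male). In that event a home-level effect, if there is one, could not be separated from the program. It is a risk of confounding, not a proven bias; section 2.6 treats gender only as a possible influence and gives no effect size.

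The conclusion assumes that:

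- homes are allocated as section 3.5.1 describes. Table 3.4 instead speaks of allocating respondents after baseline; the two need to be reconciled, and the 1-in-10 figure applies only to the home-level scheme;
- the 2013 all-resident counts still describe the homes. The sex mix of eligible residents is not given, and section 3.2 states about 130-250 residents per home, below the 292 and 278 in Table 3.1.

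**What to change.** In section 3.5.1, state that the draw is restricted so that each arm contains at least one of the three large homes and at least one of the three small ones. List the allowed allocations (18 of 20 on Table 3.1), recheck the grouping against current rosters, and draw one at random.

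The cost is one short list and one paragraph, but it must be done before allocation. A permutation test over homes would have a smallest two-sided p of about 0.11 instead of 0.10, so no attainable 5% result is lost. Some imbalance in home size remains possible: the largest allowed is 757 v 564 residents (Bedong, Cheng and Johor Bahru in one arm).

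A tighter rule is not needed. Limiting the resident-count ratio to 1.20 and the male-share gap to 5 points would keep only 10 splits, put Bedong and Kangar together in 8 of them, and raise the smallest two-sided permutation p to 2/10 = 0.20. Nothing in the documents supports those particular limits.
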